## Abstract

To reduce inequalities in children’s sport participation, studies are needed to explore ways in which children from low resource neighbourhoods can be engaged and retained in sport. GAME Community is a peer-led community sport programme which aims to promote physical activity through participation in inclusive street sports activities targeting 8–15-year-old children living in low resource neighbourhoods. The GAME Community intervention is implemented by the non-profit street sport organisation GAME. Five components support the implementation of GAME Community: (1) training of peer leaders; (2) a focus on inclusion of inactive girls; (3) parental involvement; (4) community engagement; (5) strengthened organisational support to peer leaders. In the ASPHALT II study, we aim to evaluate GAME Community and hence contribute to understanding how children growing up in low resource neighbourhoods can be engaged and retained in physical activity through participation in peer-led, community-based sport and to generate new understandings on the scale up of community interventions. The primary objective of the evaluation is to investigate the implementation of GAME Community and the programme’s reach, and to establish the functioning and mechanisms of the programme. The secondary objective is to establish the health enhancing potential of the programme. The evaluation of GAME Community involves three linked but independent studies that investigate (1) the functioning (i.e., mechanisms and processes), (2) reach, and (3) outcomes. The functioning of the five intervention components is investigated using qualitative methodologies. Programme reach will be investigated based on participant registrations. Systematic observations using a novel combination of validated tools will provide information on outcomes (physical activity level and social behaviour) during GAME Community activities. Investigating functioning, reach, and outcomes of the GAME Community intervention by using multiple methods is a strength, as different data complement and inform each other. This study will provide in-depth insights into if and how children living in low resource neighbourhoods can be engaged and retained in physical activity through participation in peer-led, community-based sport. Contributions of this evaluation include new understanding of the mechanisms and scalability of a community-based street sport intervention.

## 1. Introduction

Physical activity is important for children’s health in the short-term [1,2], as well as in the long-term, since physical activity behaviour tends to track from childhood and adolescence into adulthood [3]. Worldwide, only one out of five children adhere to international recommendations [4] and across high income countries there is inequality in physical activity with children from low socioeconomic status (SES) families being less physically active [5]. Increasing physical activity among children from low SES backgrounds is thus an important public health challenge [6], also contributing to reducing inequalities in health.

Different domains for children’s physical activity exist; recreation, transport, school, and household [7]. In the current study we will focus on recreational physical activity since participation in organised sport has proven to contribute to children’s physical activity [8] and further, sports club participation can be an important arena for children’s socialization experiences and social integration into the local community [9,10]. However, sports participation is influenced by the social environment in which children grow up, e.g., a recent systematic review and meta-analysis documented that the children living in low SES households participate less in sport [11]. Structural barriers to participation in organised sport for children from low SES families include: (i) fixed timetables for training, (ii) membership fees [9,12] and (iii) expectations of parent engagement [13]. Particularly girls from low SES families perceive barriers for participating in organised sport [12,14]. To redress inequality in sports participation among children, it is important to pay attention to alternatives to traditional sports club participation to attract and retain children from low SES families in being physically active [14,15].

Community-based health interventions are multicomponent interventions that combine individual and environmental change strategies across multiple settings aiming to promote well-being and health among population groups in a defined local community [16]. This intervention approach has the potential to effectively address community-level disparities [17]. Intervention strategies can include community-level influences on behaviour, such as local values and norms, and are more likely to generate local ownership and efficient use of resources [18]. Children spend considerable amounts of time in their community and community setting can include parents and other important influences to promote physical activity. These characteristics point towards the community setting as an important arena for promoting children’s physical activity [18].

The family also has an important influence on children’s sport participation [9,12], however, as children approach adolescence the influence of peers increases [19]. Studies have found that the social environment—being together with peers—significantly positively influences children’s physical activity behaviour [20,21]. Because of the strengthened peer influence in adolescence, peer education is a popular approach to health promotion with youth [22]. Further, peer-to-peer approaches may provide opportunities for reaching population groups who are usually considered harder to reach [23,24]. Peer-to-peer programmes build on the rationale that peer relations provide identification, credibility, trust, and role modelling influences [24]. Recent reviews have suggested that interventions based on a peer-to-peer approach may increase physical activity for children and adolescents, but more studies are needed to fully understand the potential of this approach in physical activity promotion [25,26].

To address inequality in sport participation among children in Denmark, the GAME Community programme has been developed through a partnership between the non-profit organisation GAME and research partners during 2018–2020 in the ASPHALT I study. GAME is a Danish-based street sport organisation with national as well as international activities in, Europe, Africa and the Middle East [27]. The overall aim of GAME is to offer accessible, and free-of-charge, peer-led street sport activities in low resource neighbourhoods targeting children living there. In ASPHALT I, the purpose was to improve and further develop GAME’s approach, mainly to improve stability of peer-led activities (e.g., that an activity continues over time and with few cancellations), increase retention of participants and peer-leaders (“Playmakers”), and enhance efforts to reach physically inactive groups, more specifically, physically inactive girls. A design process was conducted to better understand how to improve GAME’s existing programme. Researchers and staff from GAME participated in the process, which included fieldwork and the active involvement of girls, peer-leaders, parents, schoolteachers, and community stakeholders in the design process. The outcome of ASPHALT I was the GAME Community intervention, which is an expanded version of GAME’s previous programme. During the ASPHALT I study, it was established that it was not feasible to evaluate individual outcomes on participants in the context of GAME’s programme, as a pilot study did not generate sufficient information for this purpose. The pilot evaluation was abandoned as it was not possible to gain parental consent to evaluate individual outcomes on children as this contrasts with the GAME intervention in practice, which does not require parental consent.

The ASPHALT II study is a continued collaboration between research and practice, evaluating the functioning and outcomes of implementing the GAME Community intervention at scale in Denmark using multiple methods to overcome the challenges identified in ASPHALT I. Independent of research, GAME continues their engagement in neighbourhoods with existing GAME activities while gradually implementing additional GAME Community components. The scaling-up process consists of an increased number of components implemented in each setting rather than an increase in the number of settings targeted.

This paper presents the study protocol for the research conducted as part of the ASPHALT II study including a description and discussion of the intervention and the measurements to be used in the evaluation.

## 2. Materials and Methods

### 2.1. Study Aims

The overall aim of this study is to investigate how children living in low resource neighbourhoods can be engaged and retained in physical activity through participation in peer-led, community-based street sport. The primary objective is to investigate the implementation of GAME Community and the programme’s reach, and to establish the functioning and mechanisms of the programme. The secondary objective is to establish the health enhancing potential of the programme. The objectives are considered through three linked, but independent sub-studies described in detail further below.

### 2.2. Context

GAME is a non-profit organisation founded in 2002 with the objective of creating lasting social change through peer-led street sport and culture. One of GAME’s target areas is low resource neighbourhoods [28]. In Denmark, low resource neighbourhoods are defined based on employment rates, educational level, and criminal conviction rates among residents relative to the general population [29]. Street sport is characterised as sport activities, held in urban environments, of a non-commercial and non-professional nature (e.g., street basket, street soccer or street dance) [30]. The three main features of GAME’s programme are (1) a peer-to-peer approach in which local voluntary peer-leaders aged 16–25 years (Playmakers) are trained and supported in being role models and lead weekly diverse street sport activities for children aged 8–15 years (participants) living in low resource neighbourhoods. (2) Street sports activities are free of charge for children and do not require formal approvement by parents for children to participate. (3) The Playmakers are trained to conduct street sport activities that are inclusive and builds life skills and positive social relations among participants. In Denmark, GAME’s involvements range from neighbourhoods with one activity with few participating children to neighbourhoods with several weekly activities with large number of participants. A neighbourhood with GAME activities is defined as a GAME Zone, and thus a municipality with several low resource neighbourhoods may have several GAME Zones. Although some GAME Zones have been active for many years, GAME continuously seeks out possibilities for starting new GAME Zones. Further, some GAME Zones may be closed for a period or permanently, depending on a lack of recruitment of Playmakers, lack of facilities or lack of support from the neighbourhood. In May 2022, there were 105 educated and active peer leaders across 14 neighbourhoods (GAME Zones) in Denmark, responsible for a total of 28 weekly activities.

### 2.3. The GAME Community Intervention

GAME Community is a holistic, complex community intervention. The main component of the intervention is the weekly peer-led street sport activities, which take place at a set time and place in low resource neighbourhoods across Denmark. The implementation of these activities is supported by five synergistic intervention components: (1) training of Playmakers, (2) a focus on inclusion of inactive girls and specific activities for this purpose, (3) parental involvement, (4) community engagement, and (5) organisational support. The components, described in more detail below, will be integrated and implemented stepwise into all neighbourhoods with GAME activities during 2021–2023. The components will take different forms in different communities to match the local context. The implementation of GAME Community is dependent on partnership building in the local communities and attracting and retaining volunteer Playmakers. Therefore, local adaptation and a flexible approach is necessary in both the implementation and evaluation of GAME Community. The logic model underpinning GAME Community is shown in Figure 1. The logic model was developed during ASPHALT 1 in a collaboration between research and GAME.

#### 2.3.1. Training of Playmakers

The Playmaker training consists of an introductory course followed by four weekend camps during the following two years. Playmakers are enrolled continuously. Playmakers receive training to instruct and organise street sport activities for children within the neighbourhood. The training progress for each individual Playmaker who goes through the levels: basic, intermediate, advanced I, and advanced II, each level with corresponding learning objectives. Further, Playmakers receive tools they can use in the activities and in their everyday life with training in themes such as civic society engagement, gender equality, teamwork, life skills, conflict resolution and communication.

#### 2.3.2. Inclusion of Inactive Girls

The Playmaker training has a general focus on how to ensure an inclusive attitude and approach, particularly towards girls. Further, a group of female Playmakers are trained specifically to facilitate a new multisport activity called GAME Girl Zone. The GAME Girl Zone concept was co-developed during ASPHALT I to specifically target inactive girls and focusses less on competition and more on social relations and co-determination in the sport activities.

#### 2.3.3. Parental Involvement

To increase parent involvement and support, Playmakers and regional GAME officers participate in local social activities, e.g., BBQ-nights. Here, Playmakers and regional GAME officers introduce GAME street sport activities. Parents can meet Playmakers and discuss any potential concerns. Additionally, parents are invited to partake in national and regional events, such as GAME Finals. The programme will further collaborate with parents and parent groups who serve as informal authorities in their community to have them legitimise the Playmaker activities through their social networks, and to increase understanding in the community of the benefits of engaging in inclusive sport communities.

#### 2.3.4. Community Engagement

Before initiating activities in a neighbourhood, GAME establishes partnerships with local stakeholders, such as social housing development plans or local youth clubs. These partnerships are intended to increase involvement in the local community. The Playmakers are encouraged to participate as GAME representatives in community events or to facilitate events for the broader community with support from GAME. The purpose of such community events is to create awareness of local GAME activities to attract participants and ensure community awareness and support.

#### 2.3.5. Organisational Support

Playmakers, who often do not have any prior experience in volunteering work are supported locally by GAME zone coordinators to facilitate the overall functioning of the volunteer group and serve as role models to Playmakers. In addition, regional GAME officers function as contact people who support the Playmakers and follow up on training. These organisational structures are enforced to ensure that all Playmakers receive ongoing support and ensure that they feel confident in implementing weekly activities and avoid cancellations.

## 3. Evaluation Design and Methodology

The GAME Community programme is currently implemented at scale in Denmark by GAME but has not previously been subject to a research-based evaluation. Following Indig and colleagues’ [31] classification, the programme is thus ‘at scale dissemination’ without prior efficacy testing or real-world trial. With 20+ years of implementation, GAME’s activities have proven to be sustainable, but the health promotion outcomes are not known. With a primary focus on implementation outcomes and a secondary focus on intervention outcomes, the research design is a type 3 hybrid effectiveness-implementation design [32].

Embracing the structures and conditions of the GAME Community intervention, the evaluation design ensures that we will be able to describe the spirit of the intervention [33], determine both anticipated and unanticipated outcomes [34], and identify functioning of the programme (i.e., mechanisms and processes) [35,36,37]. As such, the overall methodology for our evaluation study is in line with recent suggestions calling for ‘holistic sense-making’ and prioritising generation of useful knowledge for practice in population health interventions [36,37]. Further, the evaluation is situated within the theory-based research paradigm for evaluating complex interventions as this paradigm is concerned with evaluating how change is brought about, embracing the interplay between mechanisms and context, which is in line with the aim of our study. We apply quantitative, qualitative, observational, and ethnographic methods to determine ’What happened’ [36] in the implementation of GAME Community. A summary of the proposed interlinked, yet independent, sub-studies that guide the evaluation is provided in Table 1.

### 3.1. Sub-Study 1: Functioning of the GAME Community Programme

We assess the level of implementation of the five GAME Community components in all GAME Zones (see Section 3.2) and their function during implementation in six neighbourhoods with high/low implementation. By comparing implementation data related to perceptions of intervention delivery in context with data on reach and retention, we investigate relationships between implementation determinants and implementation outcomes [38] to understand the functioning of the intervention.

Based on an implementation scoring of all GAME zones conducted in Fall 2022 (see Section 3.2), three GAME Zones with lowest score and three GAME Zones with highest score will be selected for a qualitative study of the functioning of the intervention. We expect this maximum variation approach to provide an information-rich comparison [39] for exploring implementation of the components and their perceived impact. We will use qualitative methods to gain insight into ways in which the five components are implemented, adapted locally, interact, and how the programme and the context into which it is implemented are mutually influenced in the process. One-on-one interviews will be conducted in 2023 with local stakeholders who are familiar with GAME Community. Moreover, focus group interviews will be conducted with Playmakers and networks representing local parents. The interviews will explore how the GAME Community elements have been implemented locally and what are the perceived outcomes of the implementation. An experienced researcher will lead the interviews following a semi-structured interview guide developed to standardize interviews between participants. To enhance trustworthiness, two researchers will code the interview data independently and reach consensus through discussion of discrepancies.

### 3.2. Sub-Study 2: Reach and Retention of Participants

For all GAME Zones, the degree of implementation of the GAME Community components will be assessed three times (in Fall 2021, 2022, and 2023), as the level of implementation at each GAME Zone is expected to either deteriorate or improve over time. Both scenarios are possible, although the intention is to achieve an increased implementation over time in all GAME Zones. Implementation degree is assessed by interviewing the regional GAME officers who oversee and support the implementation of GAME’s activities across all zones in Denmark. In 2021, comprehensive descriptions of the five GAME Community components were developed in collaboration between GAME and researchers. Based on these descriptions, the research team developed a structured interview guide to assess the implementation of the five GAME community components. For each GAME Zone, each component will be assigned a score from 1 (not implemented) to 5 (fully implemented). All GAME Zones will thus achieve a combined score between 5 and 25. By comparing GAME Zones with high and low implementation, we will explore the relationship between implementation of various programme components and programme reach in different contexts.

Simple registrations of all participants attending GAME activities across all GAME Zones will be collected from April 2022 using an app developed, managed, and owned by GAME. When a child attends an activity for the first time, the Playmaker will register the child’s attendance (activity and zone ID and date) in the app together with background information such as name, surname initials, gender, age, and current participation in organised leisure activities (assessed as current participation in sport, participation in other activities, or no current participation in organised activities). At all forthcoming GAME activities, recurring and new participant attendance will be registered. The app allows data to be linked if the same child attends different activities. Data from the app will handed over to research as an anonymised dataset. The participant registration data will allow for exploration of programme reach and retention of participants, including stratified analyses by, for example, current participation in organised leisure activities at first attendance. Moreover, registrations will provide insight into the number of activities and stability of activities over time.

To understand relations between implementation of the GAME Community components and programme reach, retention and number and stability of activities, we will investigate the functioning of the intervention by considering the role of each component in the change process [35,40]. The participant registrations related to programme reach will further be combined with qualitative data of the perceived quality of the implementation and the functioning of the programme elements. These data will be collected as an integral part of the interviews conducted during Sub-study 1 (See Section 3.1). This will provide insight into the ways in which the GAME Community elements and contextual factors attract and retain participants, including girls who did not participate in sport prior to GAME participation.

The programme’s ability to attract and retain physically inactive girls will be explored in a qualitative study utilising ethnographic approaches. Girls participating in GAME activities will be followed by participant observation and interviewed during 2023. Girls will be recruited from the three GAME Zones with the highest participation of girls to provide insights on girls’ experiences of participating in GAME Zone activities, social interactions, and interaction with Playmakers.

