### 4.1. Importance of This Study

It is important to evaluate the health enhancing potentials of practice-based interventions to determine if scarce societal resources are to be prioritised towards an intervention. In the case of GAME Community this is challenging, as individual level health outcomes cannot easily be assessed. Instead, we propose to evaluate intermediate health outcomes [45] of GAME Community (in terms of physical activity level and social behaviour and interactions) at an aggregated activity level using systematic observations. Further, we will synthesise data to evaluate implementation outcomes [38] in terms of reach (number of previously inactive children attracted, total number of children that participate and their retention) at an individual level using anonymised participant registration. Using this novel combination, the results will provide an indication of the health enhancing potential of the programme by establishing whether the participating children are attracted and retained in activities characterised by physical activity and positive social relations.

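### App registration starts in April 2022 in zones already running, with no stated way to tell children already attending from newcomers, so prior-activity status, the count of inactive children attracted and retention are mixed

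*Protocol article*

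**What the plan says.** All of the following is in the protocol article.

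- **Start of data (section 3.2).** "Simple registrations of all participants attending GAME activities across all GAME Zones will be collected from April 2022". Nothing earlier is described.
- **Entry rule (section 3.2).** "When a child attends an activity for the first time, the Playmaker will register" attendance and background information. The items named are name, surname initials, gender, age and current participation in organised leisure activities (sport, other, or none). The list is introduced as examples, so it is not closed.
- **Later records (section 3.2).** "At all forthcoming GAME activities, recurring and new participant attendance will be registered".
- **Use of the item (section 3.2).** It is offered as a stratification variable: "current participation in organised leisure activities at first attendance".
- **Programme age.** Section 2.2: "Although some GAME Zones have been active for many years". Section 3: "With 20+ years of implementation". The Introduction adds that GAME carries on in neighbourhoods where it already has activities.
- **Targets.** Section 4.1 lists the reach outcomes as "number of previously inactive children attracted", the total number of children and their retention. Section 3.2 speaks of attracting and retaining participants, "including girls who did not participate in sport prior to GAME participation".

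The strengths and limitations (section 4.2) discuss cancelled activities, the exclusion of indoor activities and subjective implementation scoring. They do not mention children already attending when the app starts.

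**The concern.** The targets concern children who join GAME and what they did before joining. The registration rule captures the first time a child appears in the app. For a child who joins after April 2022 the two coincide. For a child who was already a regular they do not, and three things follow:

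1. **Prior status.** The item asks about current participation. For a regular it is answered after months or years of GAME, so it is not a pre-GAME status.
2. **Children attracted.** A regular recruited in an earlier year enters the count as though attracted in the study period.
3. **Retention.** Children present when the app starts are a length-biased sample, because those who tried it and left are gone. Counting retention from their first record adds survivors to the newcomers.

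Reach is part of the primary objective (section 2.1), and these are its named outcomes. The data reach the researchers anonymised, so a prior status that was never asked is unlikely to be recovered later.

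**Working it through.** The article gives no reach or retention figure, no dropout rate and no share of existing attendees, so there is nothing to reproduce. All rates below are assumptions that show direction and order of size.

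**Retention: set-up.** Children enter at a steady weekly rate and are a mix of short- and long-stayers with exponential lengths of stay, means *a* and *b* weeks and entry shares *w* and 1 − *w*. Activities are taken to have run long enough before April 2022 to be in steady state.

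- 12-week retention of newcomers: N = w·exp(−12/a) + (1 − w)·exp(−12/b).
- Mean stay: M = w·a + (1 − w)·b. In steady state, the children present on the app's first day equal M weeks' worth of entrants.
- Long-stayer share among those present: L = (1 − w)·b / M.
- Their 12-week retention from first record: E = L·exp(−12/b) + (1 − L)·exp(−12/a).
- Pooled over T weeks of registration: (M·E + T·N) / (M + T).

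T = 87 weeks is an assumption: 1 April 2022 to 1 December 2023 is 609 days, within the 2022–2023 period shown in Table 1.

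**Mix A** (60% with mean 4 weeks, 40% with mean 50 weeks):

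- N = 0.6·0.050 + 0.4·0.787 = 0.345
- M = 2.4 + 20 = 22.4; L = 20/22.4 = 0.893
- E = 0.893·0.787 + 0.107·0.050 = 0.708
- Pooled = (22.4·0.708 + 87·0.345)/109.4 = 0.419, a bias of about +7 points

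**Mix B** (50% with mean 6 weeks, 50% with mean 30 weeks):

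- N = 0.5·0.135 + 0.5·0.670 = 0.403
- M = 3 + 15 = 18; L = 15/18 = 0.833
- E = 0.833·0.670 + 0.167·0.135 = 0.581
- Pooled = (18·0.581 + 87·0.403)/105 = 0.433, a bias of about +3 points

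With T = 26 weeks the same formulas give biases of about +17 points (mix A) and +7 points (mix B).

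**Wider grid.** Inputs: 20–60% long-stayers; weekly dropout hazards of 0.01–0.03 for long-stayers and 0.1–0.3 for short-stayers; three years of running before the app.

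| Registration | Pooled bias in 12-week retention |
|---|---|
| 26 weeks | +4 to +26 points |
| 87 weeks | +1 to +13 points |
| Either, same dropout rate for every child | 0 |

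**Inactive children attracted.** Let *s* be the share of first records that belong to existing attendees and *u* the share of initially inactive existing attendees who have since taken up an organised activity. Assume the same initial inactivity in both groups.

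- Inflation of the period count: (1 − s·u)/(1 − s). With s = 0.1 and u = 0.3 it is 0.97/0.90 = 1.08. With s = 0.5 and u = 0 it is 1/0.5 = 2.0.
- Relative understatement of the proportion classed as inactive: s·u, from 0 to 0.5·0.3 = 15%.

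The two mixes imply s = 22.4/109.4 = 20% and 18/105 = 17% at 87 weeks. With u = 0 the count is then inflated 1.26-fold (109.4/87) and 1.21-fold (105/87).

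**The case against.** **The logging of existing attendees is inferred.** This stands. The article does not say how a child already attending in April 2022 is entered, and its list of background items is open. The app may hold a field that the article does not mention; if so, saying so would resolve most of the point.

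**Separation is an analysis rule, which a protocol article may leave to the analysis plan.** This stands in part. Registration date and activity are collected, so a run-in can separate the groups approximately. But the article fixes the start date, the entry rule and a current-status item, and it pairs them with outcomes about status before GAME. No analysis rule recovers a pre-GAME status for existing children.

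**The effect looks larger than it is.** A reader might take 71% against 34% in mix A (E against N) as the bias. It is a contrast between two subgroups; the pooled figure over 87 weeks is 42% against 34%.

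**Everything is overstated.** A reader might infer this too, and the documents do not support it. Total length of stay is understated because the clock starts late, the proportion classed as inactive may be understated, and the total number of children participating is unaffected.

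**Old zones may score high on implementation, which would create a link between implementation and retention.** The article does not support this. The components are being introduced stepwise in all zones, and scores may rise or fall. All that follows is that contamination may differ between zones, since only some are old.

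**The work is exploratory, with no test or threshold.** True, and it lowers the stakes. A descriptive count still has to count what its name says.

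Finally, the 28 weekly activities reported for May 2022 postdate the app's start, so they do not by themselves show that activities ran before it. The statements on zone age, programme history and continuing activities do.

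**Conclusion.** The point holds. If the plan is followed as written, children already attending in April 2022 enter alongside newcomers, and a status measured after exposure is used where status before GAME is meant. That mismatch follows from the text and depends on no assumed rate; it would fall away only if the app holds an unmentioned item on earlier attendance and prior status.

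The numerical effect is unknown. Under the two assumed mixes, pooled 12-week retention is overstated by about 3 to 7 points over 87 weeks. It is more with shorter registration, up to 26 points at the extreme of the assumed grid, and nothing if dropout is homogeneous. With 10–50% existing attendees among first records, the count of inactive children attracted in the period is inflated about 1.08- to 2.0-fold. Differences between zones are plausible, but a distortion of the implementation comparison is not shown.

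**What to change.** **Preferred.** Add two items at first registration: whether, and since when, the child attended GAME before that day; and whether the child took part in organised sport before joining GAME. Report newcomers and existing participants separately. The cost is two short questions for the Playmaker and some recall error.

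**If the app cannot be changed.** Pre-specify a run-in for activities already running in April 2022, for example 8 weeks, with a sensitivity analysis on its length, since 8 is a working choice. Class children first registered in that window as existing participants. Base the newly-attracted, prior-participation and retention results on later registrants, and show existing participants in their own table. This needs no new data. It leaves fewer children in the newcomer analyses, puts some true newcomers among the existing participants, and still misclasses existing children who attend irregularly and miss the window.

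**Optional.** Name the outcome by what is measured, such as not in organised sport at first registration. This is mostly wording: the Introduction already says that the study focuses on recreational activity.

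If the app already flags earlier attendance, one sentence saying so and stating its use would settle the identification part; the current-versus-prior status item would still need attention.
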